## Abstract

**Background:**

With the development of information and communication technologies, telemedicine has been proposed as a way to improve patient management by facilitating access to appropriate diagnosis and treatment. The Paris Ile de France Regional Health Agency is currently funding a comprehensive program of telemedicine experiments. This article describes the protocols for the evaluation of the implementation of telemedicine in the Paris region.

**Methods/design:**

Over 2,500 patients have been included in eight studies addressing the use of telemedicine in the context of specific diseases or settings. Two projects are randomized controlled trials, while the six other projects are based on before-after designs (differences in differences studies). Based on the MAST model and the French national framework, we identified endpoints to assess the impact of telemedicine on five dimensions: clinical effectiveness, cost-effectiveness, security of the application, patient satisfaction and quality of life and perception of professionals.

**Discussion:**

Telemedicine encompasses a wide range of services and stakeholders, and thus study protocols must be tailored to the specific constraints and interests of the users.

**Trial registration:**

NCT02110433 (03/07/2014), NCT02157740 (05/27/2014), NCT02374697 (02/05/2015), NCT02157727 (05/27/2014), NCT02229279 (08/28/2014), NCT02368769 (02/05/2015), NCT02164747 (NCT02164747), NCT02309905 (11/27/2014).

## Background

Improving access to care for either specific populations or specific conditions or diseases is a strategic priority for the Paris Regional Health Agency (*Agence Régionale de Santé Ile-de-France*), which has authority over health care policy in the capital region of France, with a population of 12 million with a budget of €30 billion. The region has 419 hospitals and 2,000 long term and social care institutions and a total of 190,000 healthcare professionals. Its missions cover prevention, health care delivery and social care.

Telemedicine [1] has been shown to improve the management of chronic conditions, to improve decision making in acute situations [2], to compensate for local scarcity of health care resources [3] and to provide access to rare expertise [4–6]. In France, it was first legally defined in the 2009 Hospital, Patients, Health and Territories Act and the 2010 Social Security Finance Act. Telemedecine involves the remote exchange of data between a patient and health care professionals or between professionals as part of a patient’s diagnosis and health care management and is limited by decree^1^ to four types of intervention (Table 1), all of which are under the responsibility of a physician at the remote site.

**Table 1 Tab1:** Definition of telemedicine by type of provider and participant (Decree No. 2010–1229 Art.R. 6316–1 of 19 October 2010)

Type of telemedicine	Definition	On site	Remote site
Teleconsulting	Remote consultation	Patient	Physician
		Physician(s) (optional)	
		Health professional(s) (optional)	
Tele-expertise	Expert advice	Physician	Physician
Telemonitoring	Clinical, radiological or biological data interpretation	Patient	Physician
		Physician(s) (optional)	
		Health professional(s) (optional)	
Teleassistance	Medical procedure	Physician(s) and/or	Physician
		Health professional(s)	

A five-year plan with a total budget of €14 million was established by the Paris Regional Health Agency to foster the development of telemedicine in two major areas: promotion of the efficient utilization of health services in people with chronic illness and long-term conditions and improvement of access to specialized care in geographically or socially deprived populations. Chronic illnesses targeted for telehealth programs were congestive heart failure, end-stage renal failure, mental disorders and obesity. Populations were selected on the basis of need for specialized medical advice or care and access problems include neonates, nursing home residents and more generally older people with long-term conditions and social care needs, patients with acute stroke, inmates with health needs and surgical patients with suspected tumors.

The deployment of telemedicine interventions followed a competitive bidding process, and projects were selected based upon the priorities described above. The telemedicine program was also designed to create multidisciplinary teams in health and social services and to implement plans to deliver care or expertise more effectively.

National and international templates for the assessment of telemedicine projects are currently available (MAST [7], WSD [8], HAS [9]). All emphasize the need for a comparative design [10] and acknowledge the trade-off between methodological requirements to ensure internal and external validity on the one hand and feasibility, support of stakeholders and available research funds on the other. All templates also underscore the importance of using a multiple endpoint/multiple stakeholder approach. This approach may be represented by a matrix that combines clusters of endpoints with groups of stakeholders. We report here on the protocols of ongoing studies selected by the Paris Regional Health Agency to deal more efficiently with chronic conditions and to reduce social and geographic inequities in access to care, including the methodological issues raised by these studies.

## Methods/design

The research aim for each of the trials is to assess the effectiveness and cost-effectiveness of telemonitoring and teleconsulting in the management of patients with long-term health conditions, and teleconsulting or teleexpertise in the management of patients with social or geographical limitation to care access. The proposed trials are pragmatic, comparative (randomized or before-after) and assess the impact of the interventions in the context of routine delivery of care in the Paris region.

### Populations, conditions and settings

Five categories of patients are included in the telemedicine trials:
**Community-based adult patients**: The telemedicine trials concern patients suffering from heart failure or requiring care following knee or hip replacement surgery for osteoarthritis. These patients need precise and continuous management with follow-up visits or care at home.
**Institutionalized patients**: These patients are dependent elderly persons living in nursing homes without on-site access to primary and secondary care. Many consultations currently require medical transportation and the involvement of several healthcare professionals.
**Inmates:** Prisoner transportation is hazardous and costly, resulting in a significant lack of and the access to health care. The first phase of the telemedicine experiment aims to deliver dermatological expertise, followed by other specialities once feasibility has been demonstrated**.**

**Neonates:** Neonatal ICU patients are frail neonates at high risk of developing premature retinopathy. While these patients require expertise to ensure an early diagnosis, access to specialized paediatric ophthalmology is limited.
**Surgical patients needing intraoperative frozen section analysis and patients with lesions requiring complex pathological interpretation:** The scarcity of on-site and specialized pathologists to provide second opinions prompted the decision to use whole slide imaging for remote pathological examination.

Over 2,500 patients will be included in the Paris Regional Health Agency telemedicine trials.

Few exclusion criteria were defined for the studies, and patients will not be excluded based on the existence of additional physical co-morbidities.

### Interventions

We will assess interventions that fall into three of the four legal categories of telemedicine in France. Each study site has separate agreements with technology suppliers, which were chosen following tender offers by the Paris Regional Health Agency. No attempt was made to standardize the technology across study sites.
**Teleconsulting** for institutionalized and community-based patients.Two projects aim to evaluate the impact of teleconsulting for institutionalized patients and one for community-based patients. Videoconference tools, allowing real-time, face-to-face remote consultations, are installed in patient homes, nursing homes and hospitals.Telemedicine and Geriatrics in the Essonne area (TLM-TMG91 Clinical Trials NCT02164747): Prior to the availability of teleconsulting, when a nursing home resident had a serious health problem, the patient was transferred to the reference hospital emergency unit using a medical transportation vehicle with a high probability that the patient would remain for more than a few hours at the hospital. Teleconsulting allows the caregiver in the patient room to contact a physician, general practitioner or geriatrician and provide data via connected medical devices such as EKGs and blood pressure monitors. The objective of this unscheduled teleconsulting is to determine whether the patient needs to be transferred to the emergency unit or may remain at the nursing home, with or without new medications.Teleconsulting and nursing homes (TLM-EVLINE Clinical Trials NCT02157740): Scheduled specialized consultations are performed through a video conference application that allows on-site consultations instead of transporting the patient for a physician visit. Like the geriatrics project in the Essonne area, unscheduled teleconsulting is also used as a means of determining whether transfer to an emergency unit is necessary.Teleconsulting and rehabilitation at home after hip and knee surgical procedures (TLM HAD Clinical Trials NCT02229279): Patients receive a videoconference tool at home allowing the coordinated care physician to perform scheduled remote consultations, to supervise treatment and health condition after orthopedic surgery and to foster the therapeutic education of patients.

**Tele-expertise** for neonates, surgical patients and inmates.All three tele-expertise projects focus on imaging based on picture archiving and transfer.Tele-imaging to evaluate retinopathy of premature infants (TLM-DITEROP Clinical Trials NCT02157727): Screening for retinopathy of premature infants (ROP) involves highly specialized pediatric ophthalmologists, who are scarce outside of Paris. Before the recent availability of tele-expertise, it was difficult for neonatology units to follow the international recommendations for ROP screening [11]. When a specialist was not present on site, the infant was sent home with an ophtalmologist appointment. Tele-expertise allows fundus examination to be performed by a trained nurse, with pictures uploaded to a secure server and interpreted by specialized pediatric ophthalmologists.Digital slides and image transfer (TLM-Pathology Expertise NCT02374697 and TLM-Pathology Frozen Section NCT02368769): This project is aimed at performing intraoperative frozen section analysis offsite in community hospitals with the goal of obtaining the same diagnostic accuracy as with original glass slide interpretation. The same technology is used to obtain second opinions from specialized pathologists for complex pathological diagnoses using digital slides uploaded to a webserver.Teledermatology for inmates (TLM-Teledermatology Clinical Trials NCT02309905): There is a lack of dermatologists to treat skin lesions in prisons. The waiting time for an appointment often exceeds one month, and the inmate must be transported by the police to a hospital, with both the location and the date of transfer kept secret in order to prevent escapes. Furthermore, the inmate may not available for various reasons at that the time of the appointment. The objective of tele-expertise is to send images of the lesion to an offsite dermatologist, who can then prescribe an appropriate treatment for the inmate.

**Telemonitoring** for patients with heart failureHeart Failure Educational and Follow up Platform (HELP Clinical Trials NCT02110433): Connected devices for patients suffering from severe heart failure monitor weight, blood pressure and BNP (Brain Natriuretic Peptide, a biomarker of Heart Failure) and also provide an educational platform for patients and relatives. The aim is to reduce the number of adverse events, including all-cause mortality, unplanned heart failure-related hospitalizations, emergency department admissions.

### Study designs

Two studies among the eight used the individual randomized control trial (RCT) design (Table 2). Nevertheless, such designs often are neither straightforward nor ethical to implement, particularly when the professionals in charge of patient inclusion are not familiar with medical research procedures.

**Table 2 Tab2:** The eight telemedicine studies

Project	Population	Condition	Setting	Procedures	Study design	Primary Outcome Measures	Sample size
TLM-HAD	Patients with total knee replacement for Osteoarthritis or hip replacement for coxarthrosis	After surgery	Community	Teleconsulting	RCT	Mean transport duration of the specialist	154
HELP	Chronic heart failure patients	Chronic heart failure	Community	Telemonitoring	RCT	Composite end point: unplanned hospitalizations for HF/all-cause death/non-programmed emergency department admission for HF	330
TLM-EVLINE	Elderly	Emergencies, psychiatry	Nursing Home	Teleconsulting	Controlled before-after study	Number of transports to emergency services	300
TLM-TMG 91	Elderly	Emergencies	Nursing Home	Teleconsulting	Controlled before-after study	Number of days hospitalized	180
TLM-DITEROP	Premature infants	Screening for Retinopathy	intensive care unit	Tele-expertise	Controlled before-after study	Screening rate at due date	620
TLM-PATHOLOGY FROZEN SECTION	Surgical patients	Anatomic pathology	operating theatre	Tele-expertise	Uncontrolled before-after study	Time to perform the diagnostic test	224
TLM-PATHOLOGY EXPERTISE	Surgical patients	Anatomic pathology	Pathological services	Tele-expertise	Uncontrolled before-after study	Time to perform the diagnostic test	470
TLM-DERMATOLOGY	Inmates	Dermatology	prison	Teleconsulting	Controlled before-after study	Proportion of patients receiving dermatological expertise among those requiring it	100

A more pragmatic approach is the pre-post (before-after) design, where the addition of a control group reinforces the validity of the results (controlled before-after or differences in differences studies) [11]. Four studies used the latter design, as it allows greater flexibility and produces faster results while ensuring sufficient level of evidence for health authorities. Control groups could not be created for two studies, and thus we used before-after designs without control groups.

For studies with a control group, four groups will be identified:The intervention group before the implementation of the telemedicine interventionThe intervention group during telemedecine interventionThe control group before implementation of the telemedicine interventionThe control group during the telemedicine intervention

For studies without a control group, two groups will be identified:The group before the implementation of the telemedicine interventionThe group during the telemedecine intervention

Kidholm et al. suggest that an assessment based on MAST should not be started while the intervention is still being developed and needs improvement [7]; for that reason, there will be a gap of several months between the end of the “before” period and the beginning of the “after” period.

### Data sources

Various sources will be used depending on the design of the study, including web-based Case Report Forms and administrative databases, such as the Statutory Health Insurance national reimbursement database, which includes dates and costs of all medical transport, consultations and DRGs for hospital admissions. The objective was to use the medical information systems available in each setting to minimize the data collection burden.

### Outcomes

Clinical effectivenessMultiple endpoints were defined based on the particular characteristics of each telemedicine project:
o
**Impact on clinical parameters,** such as the WOMAC score [12] (TLM_HAD), will be measured.
o
**Impact on clinical management,** such as the number of lost to follow-up and time to consultation, diagnosis, prognosis or therapeutic decision.
Resource utilization, cost and cost-effectivenessImpact on health care services utilization will be measured when appropriate, particularly in the telemonitoring and teleconsulting projects. These endpoints include, for example, the number of hospitalizations, number of visits to an emergency department, number of medical transports and length of stay.The cost analysis will be performed primarily from a societal perspective, with valuation of the cost of hospital stays (including readmissions), emergency visits, outpatient visits and medical transport.Payment for telemedicine services has not been formally established in France, and thus the operating costs will be valued from the health provider perspective. These costs include the labor costs related to operation of the telemedicine intervention, professional and patient education and training, investment in equipment, the cost of building alterations and the call center, where relevant.The Incremental Cost Effectiveness Ratio (ICER) will relate the overall costs to the primary endpoint for each study.Security of the applicationWe created a registry of all problems that impede the proper functioning of the telemedicine interventions, such as unacceptable delays in obtaining required information and network or interface issues.Patient PerspectiveWe will use the WSD SUTAQ questionnaire for telemonitoring projects [13] during the last month of follow up. We previously translated that questionnaire into French following the MAST methodology: two forward translations from English to French by two different persons speaking French and English fluently, one back translation by another English-speaking native, and then an expert committee to validate the accuracy of the translation.We created a registry of all patients refusing to use telemedicine in order to assess acceptability by each target population.We will measure patient quality of life using the French version of the EQ-5D questionnaire as well as disease-specific quality of life instruments, where appropriate.Professional experienceAll professionals using one of the telemedicine applications will be requested to complete a questionnaire of their perceptions regarding it. The questionnaire is based on the MAST questionnaire and was translated into French using the MAST methodology. We will score each item using a six-item Lickert scale.

### Statistical analysis

Sample size calculations were made to demonstrate superiority (seven studies) or non inferiority (one study), based on the estimated difference and standard deviation (or on the estimated proportions) of the primary endpoint between the groups (telemedicine versus usual care). We used an alpha risk at 5 % and depending on the number of patients potentially includible, we chose a beta risk at 10 % or 20 %. The software used for calculation was found on Statstodo Website [14].

Descriptive statistics (frequencies, means ± SD) will be carried out by group, and subgroup analyses will be performed when relevant.

For the RCTs, we will assess the effectiveness of telemedicine by using the intention-to-treat principle, with the inclusion of all participants in the statistical analyses regardless of whether they completed the intervention or the follow-up measurements. Missing data will be imputed using regression imputation techniques if the population size and dataset allow it.

In the before-after studies with control groups, we will perform differences-in-differences statistical tests.

For trials in which we anticipate censored data, for example due to the high mortality risk of the specific population, we will use the log-rank test. In addition, a Cox proportional-hazards regression model will be used to limit confounding factors.

Multivariate regression analyses will be used to assess which institutional, clinical and demographic factors predict the effect of telemedicine on outcomes.

Each item in the questionnaires of patient satisfaction and health care professionals’ perceptions will be analysed separately. No global scoring will be computed.

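### The described sample-size basis is a two-group contrast, but four studies will be tested by difference-in-differences, so the stated 80% or 90% power is not supported for that test

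*Protocol article*

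**What the plan says.** All statements are in the protocol article, under Methods/design.

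- **Sizing.** The Statistical analysis section gives one rule for all eight studies, which it divides into seven superiority studies and one non-inferiority study. The sizes are "based on the estimated difference and standard deviation (or on the estimated proportions) of the primary endpoint between the groups (telemedicine versus usual care"). The error rates are also common to all: "We used an alpha risk at 5"%, and "we chose a beta risk at 10 % or 20"%, the choice resting on how many patients could be recruited.
- **Test.** The same section then says: "In the before-after studies with control groups, we will perform differences-in-differences statistical tests".
- **Groups.** Study designs states: "For studies with a control group, four groups will be identified". They are intervention and control, each before and during telemedicine.
- **Which studies.** Study designs says "Four studies used the latter design", meaning the controlled before-after design. Table 2 shows them as TLM-EVLINE (N = 300), TLM-TMG 91 (180), TLM-DITEROP (620) and TLM-DERMATOLOGY (100).

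The article gives no effect size, SD, proportion, allocation or study-specific power. It does not say whether Table 2's N covers one period or both, or whether the same people are measured in each.

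**The concern.** A two-group calculation budgets for the sampling error of two means or proportions. A difference-in-differences carries the error of four, because the control group's change is subtracted from the intervention group's change. The stated beta therefore belongs to a contrast that these four studies will not test.

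The risk lies in how a null result is read. Under Advantages and disadvantages of the proposed designs, the Regional Health Agency may propose widespread adoption on the basis of the results. The Discussion already offers weak adherence by professionals as an explanation for a negative result. If the real power of the tested contrast is well below 80%, lack of precision is a rival explanation, and the stated beta would hide it.

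**Working it through.** **Reproducing the plan's figures.** The four Ns cannot be reproduced, because no inputs are given. What follows asks what happens to the stated power if the described two-group basis was used. Assumptions: two-sided alpha 0.05 (sidedness is not stated), equal groups, common SD s, independent patients unless noted.

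**Step 1: variances.**

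- Two groups of N/2: 2s²/(N/2) = 4s²/N.
- (a) Four independent cells of N/4: 4s²/(N/4) = 16s²/N. Ratio to the two-group variance: 4.
- (b) Four independent cells, each with the full two-group n (N/2): 4s²/(N/2) = 8s²/N. Ratio: 2.
- (c) The same N people measured in both periods with correlation r: 8s²(1 − r)/N. Ratio: 2(1 − r).

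**Step 2: power for the effect that the two-group test would detect.** Power = Φ[(1.960 + z)/√ratio − 1.960], with z = 0.842 for 80% and 1.282 for 90%.

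| Case | Nominal 80% | Nominal 90% |
|---|---|---|
| (a) ratio 4 | Φ(2.802/2 − 1.960) = 28.8% | Φ(3.242/2 − 1.960) = 36.7% |
| (b) ratio 2 | Φ(2.802/1.414 − 1.960) = 50.8% | Φ(3.242/1.414 − 1.960) = 63.0% |
| (c) r = 0.3 | 65.8% | 78.2% |
| (c) r = 0.5 | 80.0% | 90.0% |
| (c) r = 0.7 | 95.1% | 98.7% |

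These results do not depend on N. With one-sided alpha, (a) gives 34.4% and 42.8%, and (b) gives 54.5% and 66.4%.

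**Step 3: check with binary outcomes**, over assumed baselines of 0.3 to 0.7 and an unpooled four-cell variance.

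| Study | Cells | Nominal 80% | Nominal 90% |
|---|---|---|---|
| DITEROP | N/4 | 27.5–29.9% | 34.8–38.2% |
| DITEROP | N/2 | 48.7–52.6% | 60.2–65.1% |
| DERMATOLOGY | N/4 | 25.3–31.2% | 31.2–39.7% |
| DERMATOLOGY | N/2 | 44.9–54.7% | 54.8–67.1% |

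**Step 4: detectable difference-in-differences at 80% power.** This uses only Table 2's N and an assumed proportion p, taken as equal in all cells for the variance: 2.80 × √[4p(1 − p)/(N/4)].

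- DITEROP, N = 620: 2.80 × √(1/155) = 22.5 percentage points at p = 0.5; 2.80 × √(0.36/155) = 13.5 points at p = 0.1 or 0.9.
- DERMATOLOGY, N = 100: 2.80 × √(1/25) = 56 points at p = 0.5; 2.80 × √(0.36/25) = 34 points at p = 0.1 or 0.9.
- For comparison, a two-group contrast at p = 0.5 detects 11.3 and 28 points.

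**The case against.** A reader might infer that all four studies are underpowered as a matter of fact. The article does not support that.

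- **The evidence is one summary sentence covering eight studies.** In the full study protocols, which are not shown, the estimated difference could be a difference in change. That is possible, but the article's wording points to the endpoint itself, or to proportions, compared between telemedicine and usual care. It mentions no change score, interaction or four-cell variance.
- **N may count one period only.** The programme total does not settle this. Table 2 sums to 2,378. Adding the four controlled studies' 1,200 once more gives 3,578. The article says over 2,500. Even on the one-period reading, different patients in each period leave 51% or 63%.
- **The same people may be measured twice.** This stands for EVLINE and TMG 91: nursing-home residents could appear in both periods, and at r of 0.5 or more no power is lost when the full two-group n is measured in each period. But neither repeat measurement nor a correlation is stated, and Study designs puts a gap of several months between the periods. This cannot rescue DITEROP, where screening by the due date is assessed once per infant. For DERMATOLOGY the article does not say.
- **The unnamed non-inferiority study might be one of the four.** If so, the null-result reading would not apply to it in the same way.
- **Nothing is miscalculated.** This is correct, and the planned test and its type I error are unaffected. The fault is a mismatch between the described sizing and the described test.

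**Conclusion.** The point holds as a mismatch: the power the article states belongs to a two-group contrast, and it is not supported for the difference-in-differences test planned in these four studies.

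The size is conditional. With equal cells and different patients in each period, nominal 80% (90%) becomes about 29% (37%) if N is shared over four cells, and about 51% (63%) if every cell has the full two-group n. Confidence is highest for DITEROP. For EVLINE and TMG 91 the loss could be nil, depending on an unstated overlap and correlation. The detectable differences of 22.5 and 56 points are the largest-variance case (p = 0.5) and fall to about 13.5 and 34 points at p = 0.1 or 0.9. No study's true power can be derived from the article.

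**What to change.** For each of TLM-EVLINE, TLM-TMG 91, TLM-DITEROP and TLM-DERMATOLOGY:

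1. State what Table 2's N counts and how it divides over the four groups.
2. State whether the same people are measured in both periods and, if so, the assumed before-after correlation.
3. Replace the blanket beta with the power, or the minimum detectable effect, of the group-by-period contrast, computed from the actual cell sizes, cell variances and any such correlation.
4. Name the non-inferiority study. If it is one of the four, give its power on the same contrast.
5. Report null results against the recomputed figure.

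The cost is a recalculation and a few lines of protocol or SAP text. No patients are added, which matters because Perspectives says these studies were already including patients by December 2014. The stated power may become less favourable.

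Lengthening the before period with database records should not be proposed yet. Data sources and Ethics approval refer to national reimbursement and population-wide health data, while Withdrawn designs says no data were collected routinely before implementation. Those statements must be reconciled first.
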